### Outcome measures

Outcome measures to be assessed at baseline, after the completion of the exercise intervention, and at week 12 of the follow-up period include:*Trunk extensor muscle cross-sectional area (primary outcome):* magnetic resonance imaging (MRI) will be performed with a 0.25-Tesla Musculoskeletal MRI system (Esaote G-Scan Brio, Genoa, Italy) to acquire contiguous transverse T-1 weighted spin echo image slices in the trunk region between L2 and L5, with a slice thickness of 10 mm. To ensure the consistency within/among subjects, the isocenter will be positioned at the midpoint of the L3/L4 intervertebral disc. The number of the slices will vary across participants to cover the region of our interest. Prior to all MRIs subjects will lie supine for at least 15 minutes to minimize the effects of fluid shifts on volumetric calculations. The post-testing MRI scan will be obtained 3 days after the final training session to minimize the effects of exercise-induced fluid shifts. After scanning, images will be transferred to a computer for calculation of CSA. Muscle anatomical CSA will be calculated for (1) the quadratus lumborum, (2) iliocostalis lumborum/longissimus thoracis (these two muscles will be grouped due to the difficulty in defining distinct fascial borders in some subjects), and (3) the multifidus. This calculation will be based on an average of three slices obtained from the center of the respective muscles*Trunk extensor muscle strength (secondary outcome):* participants will perform three maximum isometric TE contractions on a customized lumbar extension dynamometer (MedX; Ocala, FL, USA) at 36° from full extension (additional trials will be provided as needed if subjects continually exert more force with each trial). Each contraction will last approximately 5 seconds with at least a 60-second interval. Muscle strength will be defined as the highest value recorded in any trial. Muscle strength for leg extensors, plantar flexors, and elbow flexors will also be assessed to permit the calculation of the training intensity for the exercise programs. For all strength assessments, time-series torque signals will be collected at 500 Hz by a Biopac MP150 system (Biopac Systems Inc., Santa Barbara, CA, USA)*Trunk extensor muscle endurance (secondary outcome):* participants will perform a sustained, submaximal isometric trunk extension contraction at 20 % of their baseline muscle strength until volitional task failure on a customized lumbar extension dynamometer at 36° from full extension. During this task, the target will be displayed on a computer monitor placed in front of the participant and the time to task failure will be quantified. The time-series torque signal will be collected at 500 Hz by a Biopac MP150 system (Biopac Systems Inc., Santa Barbara, CA, USA)*Pain and perceived disability (tertiary outcomes):* a 0–10 numerical pain rating (NPR) scale will be used to quantify LBP. The Roland Morris Disability Questionnaire, which consists of 24 items related to LBP, will be used to quantify perceived disability [67]. These data will be used to calculate the rate, duration, pain intensity, and disability of LBP recurrence during the follow-up period. To analyze LBP recurrence, we will first define an episode of LBP as a period of pain in the lower back lasting for more than 24 hours, preceded and followed by a period of at least 1 month without LBP. This definition is consistent with that suggested by de Vet and colleagues [68]. We will then compute the rate of LBP recurrence as the number of episodes per quarter, duration as how long on average each episode lasted within each participant, and intensity as the mean and maximum pain/disability scores over the follow-up period as well as during an episode of LBP occurrence

Other outcomes:*Body composition.* Dual-energy X-ray absorptiometry (DEXA: Hologic Discovery QDR model Series, Waltham, MA, USA) will be performed to assess whole body and regional lean mass as well as whole body and regional fat mass. Participants will be instructed to adequately hydrate prior to the body composition assessment. These data will permit us to determine the effects of the exercise interventions on increasing appendicular lean mass and examine whether individuals with the greatest increases in appendicular lean mass exhibited the greatest “cross-transfer” of effect to the TE CSA (measured via MRI)*Treatment acceptability*. Treatment acceptability will be determined by administering the Treatment Evaluation Inventory survey at the end of every fourth exercise session [69]

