1. Participate in progressive resistance exercise within the previous 24 weeks prior to screening 2. Experienced limb amputation (except for toes) and/or any fracture within 24 weeks 3. Have a personal history of the following neurological disorders: Alzheimer’s disease, amyotrophic lateral sclerosis, multiple sclerosis, Parkinson’s disease, or stroke 4. Have a personal history of the following cardiorespiratory disorders: congestive heart failure, myocardial infarction, or peripheral vascular disease 5. Have conditions (e.g., myasthenia gravis, myositis, muscular dystrophy or myopathy, including drug-induced myopathy) leading to muscle loss, muscle weakness, muscle cramps or myalgia 6. Have a personal history of the following musculoskeletal disorders: rheumatoid arthritis, spinal or pathological fractures, scoliosis, spondylolisthesis, avascular necrosis or osteonecrosis, severe osteoarthritis. (Including a history of spinal surgery or a hip arthroplasty). 7. Have a personal history of any of the following conditions or disorders not previously listed: diabetes, fibromyalgia, active cancer, severe obesity (i.e., body mass index greater than 35 kg/m^2^), clinical depression (i.e., subjects who score 24 or higher on the Center for Epidemiology Depression Scale) 8. Have chronic or relapsing/remitting gastrointestinal disorders such as inflammatory bowel diseases, irritable bowel syndrome or gastrointestinal infections within 28 days of screening 9. Have an acute viral or bacterial upper or lower respiratory infection at screening 10. Have moderate or severe chronic obstructive pulmonary disease 11. Report back pain greater than 4 (on a 10- point numerical pain rating scale) at screening 12. Have a leg length discrepancy >3 cm 13. Exhibit abnormal or uncontrolled blood pressure (BP) at the screening visit (i.e., diastolic BP >100 and/or systolic BP >160 mmHg). If taking anti-hypertensive medication, have to be on stable doses of medication for more than 3 months 14. Exhibit abnormal electrocardiogram findings indicative of left ventricular hypertrophy (based on Cornell voltage criteria) at the screening visit 15. Have a current or recent history (within 1 year of screen) of heavy alcohol consumption (men ≥21 drinks/week, 4 drinks/day; women ≥14 drinks/week, 3 drinks/day) or drug abuse 16. Have a current or previous use of any drugs known to influence muscle mass or performance within 24 weeks 17. Report being pregnant, lactating, or that they anticipate becoming pregnant in the next year 18. Report unexplained weight loss over the past month (>10 lbs) 19. Report they have pending litigation related to an episode of LBP or are receiving any type of disability services 20. Use of systemic glucocorticoids within 12 weeks prior to screening 21. Report having received any treatment for LBP by a health care practitioner in the past 6 weeks22. Have contraindications for exposure to a magnetic field

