### Study time line

A table of events for study is illustrated in Table 2. This study will have a screening/baseline assessment period of 21 days, a 10-week exercise training period and a 36-week follow-up period after the last exercise session. Participants will visit Ohio University’s Clinical and Translational Research Unit facilities prior to the intervention for their baseline assessments (detailed below). Following completion of the 10-week exercise intervention, participants will be re-assessed (primary endpoint). Next, participants will enter a 36-week follow-up period during which all outcomes will be assessed 12 weeks (±7 days) after the completion of the exercise program and once every 4 weeks during the follow-up period, they will be contacted via email to log onto a secure web-based survey system where they will be asked to rate their perceived disability (Roland Morris Disability Questionnaire [67]) and back pain (0–10 numerical pain rating scale) over the past 14 days. These data will be used to calculate the rate, duration, pain intensity, and disability of LBP recurrence during the follow-up period.

**Table 2 Tab2:** Schedule of events for all groups

Study procedure	Screen/baseline period		Intervention period					Follow-up		
	Screen visit 1	Baseline visit 2	Visits 3–6^b^	Visits 7–10^b^	Visits 11–14^b^	Visits 15–18^b^	Visits 19–22^b^	Visit 23^a^	Visit 24^a^	Non-visit surveys
Day (window, ± days)	−21 to −1	−21 to −1	1 − 14	15 − 28	29 − 42	43 − 56	57 − 70	71 ± 4	154 ± 7	Once every 4 weeks^c^
Screening/baseline:										
Informed consent	X									
Inclusion/exclusion	X									
Medical history	X									
Weight	X							X	X	
Height and demographics	X									
PAR-Q, IPAQ	X									
Electrocardiogram	X									
Sorensen test	X									
Randomization			X							
Exercise sessions:										
Exercise^d^			X	X	X^d^	X	X			
Efficacy:										
MRI		X						X	X	
DEXA		X						X	X	
Strength		X						X	X	
Endurance		X						X	X	
Pain and disability	X	X	X	X	X	X	X	X	X	X
Treatment acceptability			X	X	X	X	X			

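### The recurrence rate gives continuous or closely spaced back pain the same zero as no pain at all, so its group comparison can point the wrong way if the arms differ in persistent pain

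*Protocol article*

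**What the plan says.** Under Outcome measures, the article requires an episode to exceed 24 hours of lower-back pain. The episode must also be "preceded and followed by a period of at least 1 month without LBP". The article then builds three measures:

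- Rate: "We will then compute the rate of LBP recurrence as the number of episodes per quarter".
- Duration: "duration as how long on average each episode lasted within each participant".
- Intensity: "intensity as the mean and maximum pain/disability scores over the follow-up period as well as during an episode of LBP occurrence".

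Statistical analyses compares these measures between the groups with linear mixed-effects models. The observation window is "a 36-week follow-up period after the last exercise session" (Study time line), with nine web surveys at 4-week intervals (Table 2, footnote c).

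On entry pain, exclusion item 11 in Table 1 removes those who "Report back pain greater than 4 (on a 10- point numerical pain rating scale) at screening". Inclusion item 2 asks for two or more episodes in the past 12 months, at least one of which restricted activity. It does not require a pain-free month around those episodes, and no pain-free run-in is stated.

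**The concern.** A recurrence count should rank participants by how they fare. This one does not. Zero is its lowest and so most favourable value, and two opposite kinds of participant reach it: those who never hurt and those who never stop hurting. People whose bouts are less than a month apart also score zero, and a bout that has not resolved by the end of follow-up adds nothing.

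The flaw lies in applying the definition to the admitted population, and recording pain daily would not remove it. If training with blood flow restriction (BFR) turned persistent pain into occasional short flares, that arm's recurrence rate would rise.

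The effect spreads to two related measures. Episode duration and within-episode intensity do not exist for a participant with no episode, so the persistent cases drop out of those comparisons.

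The article presents the trial as a source of effect sizes, recurrence included, for planning later studies. A recurrence effect with the wrong sign could be carried into that planning.

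**Working it through.** The document gives no recurrence rate to reproduce. The check applies the written definition to assumed pain patterns.

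**Inputs from the document:** pain for more than 24 hours; at least 1 month without LBP on each side; follow-up of 36 weeks = 36 × 7 = 252 days; at least 16 participants per group.

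**Conventions assumed:** a bout counts if it lasts at least 2 days and has at least 30 pain-free days before and after it. One quarter is 91 days, so follow-up is 252/91 = 2.77 quarters, and rate = episodes / 2.77.

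**Step 1. Individual patterns over 252 days**

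| Assumed pattern | Pain days | Episodes | Per quarter |
|---|---|---|---|
| Never in pain | 0 | 0 | 0.00 |
| Continuous pain | 252 | 0 | 0.00 |
| Continuous from day 100 | 152 | 0 | 0.00 |
| 7 days in every 28 | 63 | 0 | 0.00 |
| 2 days in every 21 | 24 | 0 | 0.00 |
| One 3-day bout | 3 | 1 | 1/2.77 = 0.36 |
| 3-day bout every 60 days | 12 | 4 | 4/2.77 = 1.44 |

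A participant with 3 pain days scores worse than one with 252.

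**Step 2. Group means when the arms differ in persistent pain.** Assume 16 per arm, 0 episodes for each persistent participant and 2 for every other. Let every BFR participant be episodic (mean 2.00) and let m controls be persistent. Control mean = 2(16 − m)/16. For m = 0, 2, 4, 6 this gives 2.00, 1.75, 1.50, 1.25. The control arm's rate looks better as more of its members have persistent pain.

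**Step 3. Size against the persistent share.** Assume 40% of controls are episodic with 2 episodes each, a share p is persistent, and the rest have none. Control mean = 0.40 × 2 + p × 0 = 0.80. Let BFR move half of the persistent group to one short episode each and change nobody else. BFR mean = 0.80 + p/2.

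| Persistent share p (assumed) | Control mean | BFR mean | Ratio |
|---|---|---|---|
| 0% | 0.80 | 0.80 | 1.00 |
| 10% | 0.80 | 0.85 | 1.06 |
| 40% | 0.80 | 1.00 | 1.25 |

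The only change in this scenario is an improvement, yet the rate rises whenever p is above zero.

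**Step 4. Measures that escape.** Mean and maximum pain and disability over the whole follow-up need no episode, and they register the continuous-pain participant as badly off. The reversal is confined to the episode rate; duration and within-episode intensity are affected because they are undefined without an episode.

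**The case against.** The strongest reply is that the plan already contains what is needed. Whole-follow-up mean and maximum scores are planned and compared between groups. If BFR turned persistent pain into short flares, mean pain would fall and show the benefit. This stands. A reader might infer that the trial cannot answer its tertiary pain and disability questions. The document does not support that, because only the episode-based measures are exposed.

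Second, the population is selected towards episodic pain: two or more episodes in 12 months, current pain no higher than 4, no recent LBP treatment, no disability services or pending litigation. Persistent pain is therefore possible but not shown to be common. This also stands, and it limits the claim to what can happen. It does not remove the problem, since the screening rating is a single reading and nothing requires a pain-free month.

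Third, a treatment might also prevent episodes in episodic participants and so still lower the rate. That is true, and the sign depends on the mix.

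Fourth, a reader might count the unconfirmable last month (about 4 of 36 weeks, 11%) as further evidence of a reversed comparison. It is not. It applies to both arms alike and does not by itself change the sign.

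Fifth, the article describes its definition as consistent with a published one, and handling of unresolved pain could sit in an analysis plan. But a definition that suits the description of an episode need not suit a between-group count. The problem is also more than a missing detail, because the stated rule as written yields the zero.

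**Conclusion.** The point holds for the recurrence rate and, through undefined values, for episode duration and within-episode intensity. The tie between continuous pain and no pain follows from the wording and needs no assumption about frequency. The consequence for the group comparison is conditional: the rate can point the wrong way if the arms differ in persistent or closely spaced pain.

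The document gives no persistent share, so no single size can be claimed. Under the scenario shown, the spurious increase is nil at 0%, about 6% at 10% and 25% at 40%. A reader might take the 25% as an expected bias, but it is only the result at one assumed share.

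The stakes are moderate. Recurrence is a tertiary outcome in an exploratory pilot, and the primary outcome, muscle cross-sectional area, is untouched. The change is still worth making, because estimating effects for later trials is the stated purpose.

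**What to change.** Amend the outcome definition as follows:

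1. Do not score participants without a qualifying pain-free month as recurrence-free.
2. Report persistent LBP, meaning never pain-free for 1 month during follow-up, as a separate unfavourable category by group.
3. Present the episode rate together with that category, the proportion of the nine follow-up surveys with LBP present, and the planned whole-follow-up mean pain. Interpret the rate only alongside them. The survey proportion and mean pain also pick up the participant whose pain begins partway through follow-up and does not resolve, whom the category alone would miss.

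The recurrence rate can remain a named outcome; demoting it to a purely descriptive result is not needed.

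The cost is wording only, with no new visits or data. The downside is that the surveys see only part of each 28-day interval. The recall window is 14 days in Study time line but 7 days in Table 2, footnote c, which is 14/28 = 50% or 7/28 = 25% coverage. These two statements must be reconciled first, and any persistent-pain category derived from the surveys is approximate to that extent.

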^a^Efficacy outcome measures may be collected in more than one visit if needed and/or preferred. ^b^Exercise training sessions will be performed twice per week with at least 1 day between the exercise sessions. Once every 2 weeks, prior to performing the exercise, the pain, disability, and treatment acceptability outcomes will be assessed (i.e., pain, disability, and treatment acceptability will be quantified on visits 6, 10, 14, 18, and 22). ^c^On days 98, 126, 154, 182, 210, 238, 266, 294, and 322 ± 3 days study participants will be contacted via email to log onto a secure web-based survey system where they will be asked to rate their perceived disability (Roland Morris Disability Questionnaire) and back pain (0 − 10 numerical pain rating scale) over the past 7 days. ^d^One of the exercise training sessions will be replaced by the strength assessment sessions during week 5.

*DEXA* dual-energy X-ray absorptiometry, *IPAQ* International Physical Activity Questionnaire, *MRI* magnetic resonance imaging, *PAR-Q* Physical Activity Readiness Questionnaire

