### Sample size calculation

We assume an attrition rate of 10 % for the muscle CSA and muscle function outcomes immediately following training and 20 % for the pain and disability outcomes at follow-up, both assuming missing at random. We also assume that three covariates (e.g., pre-training value, sex, age, etc.) will explain an additional 30 % of the unexplained variance for all outcomes (correlation between the baseline volume and the percentage change in our pilot data was *r* = −0.57). Significance will be set to 0.05, and no *p* value adjustment will be applied due to the exploratory nature of the study. For the primary outcome, our pilot data indicate that the control exercise group and the BFR exercise group differ in CSA percentage change by 3.1 ± 3.1 %. The standard deviation and adjusted effect size derived from our small sample of pilot data (*n* = 7) are, as expected, imprecise: 95 % confidence interval (CI95) around the standard deviation (SD) = 2.0–6.9; around Cohen’s *d* = −1.1–3.2. As such, the primary goal of this study is to gather critical preliminary data to accurately and precisely estimate the population effect size so that future studies will be adequately powered. We will achieve accurate estimation by minimizing potential bias through designing a better study: blinding, randomization, and examining missing patterns. We will achieve more precise estimation by more than doubling the sample size to at least *n* = 16/group (and will enroll up to 20/group depending on resources). This sample size will narrow the range of CI95 around the estimated population effect size by over 60 %, from 3.2–(−1.1) = 4.3 to 1.9–0.3 = 1.6. This sample size will also allow us to achieve a desired power for the future study more than 95 % of the time by overestimating the population SD [70]. For reference and planning purposes we have conducted a power analysis. To make our test conservative, we estimated a treatment effect of 2.5 %. If we assume its SD to be in the range of 3.0–6.0, which will be translated into adjusted Cohen’s *d* of 0.42 to approximately 0.83 the corresponding sample size to achieve a power of 0.8 would be 26–100 per group, taking attrition into consideration. Likewise, required sample sizes would be 30–65 per group for trunk strength and endurance, assuming 6.0 ± 8.0–12.0 % improvements, and 41–112 per group in pain and disability averaged over the course of a year assuming 2.0 ± 3.0–5.0 and 4.0 ± 6.0–10.0 reductions in pain and disability, respectively.

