
### Statistical analyses

For the three trunk extensor-related outcomes (i.e., size, strength, and endurance), we will compute a percentage change and will test a difference in group means using linear mixed-effects (LME) models with covariates included to increase the precision of effect-size estimation. To analyze LBP recurrence, we will compute the rate of LBP recurrence, average duration of a LBP episode, and intensity as the mean and maximum pain and disability scores over the follow-up period as well as during an episode of LBP occurrence. We will test whether the groups differ in these measures with LME models. We will assess potential bias due to loss to follow-up by examining whether characteristics measured at baseline and immediately following the training will predict attrition. We will perform exploratory intention-to-treat analyses (ITT), of all randomized study participants who have baseline assessments and estimate parameters based on last observation carried forward as well as maximum likelihood estimation. We will also perform exploratory per-protocol analyses (PPA) where we will exclude study participants who (1) fail to attend 75 % of their exercise training sessions, (2) receive prohibited concomitant interventions, or (3) develop an exclusionary medical condition while on study protocol.

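### The maximum follow-up pain or disability score depends on how many surveys a participant answers, and collapsing scores to one value per person before modelling removes the protection that maximum likelihood would give

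*Protocol article*

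**What the plan says.** Under Outcome measures, the protocol article takes "intensity as the mean and maximum pain/disability scores over the follow-up period as well as during an episode of LBP occurrence". Statistical analyses repeats the definition ("intensity as the mean and maximum pain and disability scores over the follow-up period as well as during an episode of LBP occurrence") and continues: "We will test whether the groups differ in these measures with LME models". The quantities to be modelled are therefore the derived summaries, not the separate survey scores.

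The scores come from nine surveys, scheduled in the footnotes to Table 2: "On days 98, 126, 154, 182, 210, 238, 266, 294, and 322 ± 3 days". They are self-completed; under Study time line, participants are told that "they will be contacted via email to log onto a secure web-based survey system".

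Sample size calculation expects attrition of "20 % for the pain and disability outcomes at follow-up, both assuming missing at random". For missing data, Statistical analyses offers exploratory intention-to-treat analyses that "estimate parameters based on last observation carried forward as well as maximum likelihood estimation", and a check of whether baseline and post-training characteristics predict attrition.

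**The concern.** The largest of nine scores from a person tends to exceed the largest of four from the same person, even when the pain process is identical. A maximum over whatever was answered therefore partly measures survey completion. If one arm answers fewer surveys, its worst pain looks milder for that reason alone.

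The mean raises a different and weaker issue. Missing at random allows dropout to depend on earlier scores. A mixed model fitted by maximum likelihood to the individual scores can use those earlier scores. A model fitted to one collapsed value per person cannot, because it no longer sees which surveys are missing.

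This bears on the trial's stated aim, which is accurate estimation of effect sizes for planning later studies.

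**Working it through.** The plan gives no figure for the maximum, so there is none to reproduce. The inputs from the protocol article are nine surveys, 20 % attrition, at least 16 participants per group, and a planning effect of 2.0 points (SD 3.0 to 5.0) for averaged pain. It gives no distribution for the survey scores, so those below are assumptions. The figures are for the 0–10 pain scale; disability was not simulated.

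**1. Expected maximum by number of surveys answered.** Scores were simulated for 200,000 participants per scenario, with underlying mean 2, SD 2 or 3, within-person correlation 0.3, 0.5 or 0.7, and no change in pain over time. Two of the six scenarios:

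| Surveys answered | 9 | 7 | 5 | 3 | 1 |
|---|---|---|---|---|---|
| Maximum, SD 2, correlation 0.5 | 4.10 | 3.91 | 3.65 | 3.21 | 2.16 |
| Maximum, SD 3, correlation 0.5 | 5.14 | 4.87 | 4.49 | 3.87 | 2.45 |

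The mean score stays at about 2.16 and 2.44 whatever the count. Over all six scenarios:
- five surveys instead of nine lower the expected maximum by 0.34 (3.64 − 3.30) to 0.79 (5.71 − 4.92);
- three instead of nine lower it by 0.67 (3.64 − 2.97) to 1.55 (5.71 − 4.16).

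**2. Deficit per dropout, δ.** With 20 % of participants leaving at a random survey, the group's average maximum falls by 0.11 to 0.25. Dividing by 0.20 gives δ = 0.55 to 1.25 points per dropout. A second set of assumptions (person mean 2 to 3, between-person SD 1.0 to 1.5, within-person SD 1.0 to 2.5) gives 0.52 to 1.24. Skipping surveys at random without dropping out also matters: the maximum falls by 0.14 to 0.31 if 20 % of surveys are skipped, and by 0.32 to 0.75 if 40 % are.

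**3. Bias in the group difference.** Bias = (attrition in one arm − attrition in the other) × δ.
- Equal attrition: (0.20 − 0.20) × δ = 0.
- 10 % versus 30 %, which averages to the planned 20 %: 0.20 × 0.52 = 0.10, up to 0.20 × 1.25 = 0.25 points.

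**4. The mean.** With surveys missing at random in the simple sense (unrelated to pain), the bias is about 0.00. When dropout follows high scores, which missing at random permits, the collapsed mean moved up by 0.03 to 0.14 with 79 to 90 % completing all surveys, and by up to about 0.2 under other assumed values. When painful surveys are skipped, it moved down by 0.04 to 0.21. That second mechanism is not missing at random, so maximum likelihood would not remove it either.

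**5. The stated safeguards.**
- Last observation carried forward repeats a score already observed, so the maximum is unchanged.
- Maximum likelihood on the summary sees a complete value for anyone who answered at least one survey.
- The attrition check describes who leaves; it does not alter the endpoint.

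**The case against.** Several counter-arguments have force.

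- **Unequal attrition is not shown.** The article gives no split by arm. Both arms exercise to failure on an otherwise identical programme, the surveys come after training ends, and no significant adverse-event problem is anticipated. This stands: the 10 % versus 30 % split is an illustration. It remains possible, since blinding is described only for outcome assessors and the cuffs reveal the arm.
- **The bias is small against the noise.** With 16 per group and the planned SDs, the standard error of a group difference is 3.0 × √(2/16) = 1.06 to 5.0 × √(2/16) = 1.77, so the bias is 0.10/1.77 = 0.06 to 0.25/1.06 = 0.24 standard errors. Those SDs are for averaged pain. With the simulated SD of the maximum, the scenarios run from 0.11/(1.79 × √(2/16)) = 0.17 to 0.25/(2.17 × √(2/16)) = 0.33. This also stands: the bias would rarely decide a test in this trial.
- **Naming mixed models might imply that repeated scores are analysed.** The text applies them to the derived measures, and a mean or maximum over the whole follow-up is one value per person. The objection fails on the wording.
- **A minimum number of surveys is analysis-plan detail.** Agreed, and its absence is not the point. The point is the summary that the article fixes.
- **Clinic scores add information.** Table 2 also lists pain and disability at both follow-up visits. Counting them would change the number of scores, but not the dependence on that number.

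A reader might also infer that missing surveys make the mean look milder. They do not, because the mean can move either way. Nor should the 0.5 to 1.25 points be set against the 2.0-point planning effect: the first is the deficit of one dropout's maximum, the second a group difference in averaged pain.

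**Conclusion.** The point holds in limited form. The downward dependence on survey count is built into the maximum and is not repaired by the stated missing-data methods. It becomes a bias between groups only if response differs by arm. Its size is then about 0.10 to 0.25 points under an assumed 10 % versus 30 % attrition and assumed score distributions. For the mean, the loss is the protection that maximum likelihood gives when dropout depends on observed scores, worth up to about 0.2 points under assumed values.

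The documents do not support saying that the comparison will be biased, or that the trial's main conclusion is at risk. Pain and disability are tertiary outcomes of an exploratory pilot, and the primary outcome is untouched. The weight is minor to moderate.

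**What to change.** Fit the planned linear mixed model to the individual four-weekly pain and disability scores, with group, survey time and baseline score. Report the group difference averaged over the nine surveys as the intensity result. This corresponds to the averaged quantity in Sample size calculation and lets maximum likelihood work under the missing-at-random assumption stated there.

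Keep the maximum as a description, shown with the number of surveys answered or among complete responders. Alternatively, compare it with an adjustment for the number answered.

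The data and model family are unchanged. If the maximum becomes descriptive, the cost is that it is no longer a tested comparison. Replacing it with the share of surveys above a pain threshold is not needed for this repair, and would measure frequency rather than worst intensity. The within-episode summaries are not covered by this change and would need their own statement.
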